### Participant Timeline

Participants will be directed according to the timeline in Figure 3. The enrollment of study participants will take 7 days from the eligibility screen until the allocation. There will be 2 measurement sessions in this study with a time interval of 7 days. The SPF measurement for each session will be carried out 24 hours after the session.

**Figure 3 figure3:**
[figure not shown]
The schedule of enrollment, interventions, and assessments. SPF: sun protection factor.

### Sample Size Estimates

The calculation of the sample size was carried out using the continuous variable noninferiority test formula and the comparison of the mean of the 2 groups in pairs. From the 2 formulas, the largest number of samples was taken for further use in research. Based on the previous clinical trial and risk of dropout, we estimated a minimum sample size of 22 participants in each group. We calculated the sample size using the difference in the average decrease in SPF levels that is considered significant, based on the clinical judgement set by the researchers (ie, 5). In total, 22 experimental subjects and 22 control subjects will be adequate to reject the null hypothesis that the population means of the experimental and control groups are equal with a probability (power) of 0.9. The type I error probability associated with this test of this null hypothesis is 0.05.

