### Outcomes

This study will provide mean differences in SPF by 4 to establish noninferiority with a 95% lower confidence limit. The hypothesis will be tested using paired samples *t* test or Wilcoxon test to assess the difference of SPF levels in each group between organic and inorganic sunscreens. The difference in SPF level will be declared to be no different if the *P* value for the paired *t* test or Wilcoxon test is >.05, and the upper limit of the CI does not exceed 4 SPF level. The persistence of organic and inorganic sunscreens is assessed using the following parameters: (1) the MED is defined as the dose of UV radiation that induces just perceptible erythema on exposed skin 24 hours after irradiation. This MED result will be stated in mJ/cm^2^. (2) SPF is defined as the ratio of MED between protected and unprotected skin areas. The average SPF value from each type of sunscreen will be computed. The SPF value will be rounded up to one decimal in the index unit. (3) Persistence of SPF is defined as the lowest differences of SPF value before and after 1.5 hours swimming, stated in index unit.

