### Data Management and Statistical Methods

All data obtained on the research status will be recorded for further coding. The collected data will be analyzed using SPSS (version 20.0; IBM Corp). The analysis will be carried out in 2 stages: descriptive and inferential analyses. In descriptive analysis, each variable is explained according to the type of data. The distribution of numerical data is assessed by looking at the normality value. The distribution of normal data is displayed with the mean and SD values. Categorical data are displayed in the form of frequency and percentage tables. In the inferential stage, the hypothesis will be tested using paired *t* test or Wilcoxon test to assess the differences in the decrease in SPF levels in each group of inorganic and organic sunscreens, and between the 2 groups. We used a 1-sided CI approach in the statistical analysis. The mean difference in SPF will be no different if the *P* value for the paired *t* test is >.05, and the upper limit of the CI does not exceed 4 SPF.

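### The 90% power is stated for a difference of 5 against equal means, but noninferiority is judged at 4 and no power at 4 is given; carried over, it is roughly 0.74 to 0.84

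*Protocol article*

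**What the plan says.** Sample Size Estimates gives one planning difference: "the difference in the average decrease in SPF levels that is considered significant, based on the clinical judgement set by the researchers (ie, 5"). It attaches the power to a test of equality, with 22 on each side: "population means of the experimental and control groups are equal with a probability (power) of 0.9". On error it says: "The type I error probability associated with this test of this null hypothesis is 0.05". It does not say whether that 0.05 is one-sided or two-sided.

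The same section reports that the sample size was worked out "using the continuous variable noninferiority test formula and the comparison of the mean of the 2 groups in pairs", and that the larger result was used. It says the 22 allows for dropout. It gives no SD, no dropout rate and no inputs or result for the noninferiority formula.

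The decision rule uses another number. Outcomes says: "This study will provide mean differences in SPF by 4 to establish noninferiority with a 95% lower confidence limit". Data Management and Statistical Methods requires that "the upper limit of the CI does not exceed 4 SPF", together with a P value above .05, and says the CI approach is one-sided. Study Design and Setting confirms that both products are applied to the same person.

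**The concern.** Two things differ between the power statement and the decision rule. The threshold is 5 in one and 4 in the other. The null is equal means in one; in the other it should be that inorganic sunscreen loses at least 4 more SPF units than organic. The 0.9 therefore does not describe the chance that the trial meets its own criterion.

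Power at the margin tells a reader how to weigh a failure to show noninferiority. If the products are truly equal, the article implies a 10% chance of missing noninferiority; the calculation below puts it higher. Two unreconciled numbers also leave the margin open to question, because an upper limit between 4 and 5 fails one and passes the other.

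**Working it through.** **Inputs from the article.** n = 22 pairs, difference 5, power 0.90, alpha 0.05 with sidedness not stated (Sample Size Estimates); margin 4 and P > .05 (Outcomes; Data Management and Statistical Methods); one-sided CI (Data Management and Statistical Methods); paired design (Study Design and Setting).

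**Assumptions.** True difference 0, and the 0.90 at 5 applies to 22 pairs. The second is relaxed in step 5.

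**1. The plan's own figure.** The 22 cannot be reproduced forward, because no SD is given. Instead, solve for the SD of paired differences that gives exactly 0.90 at a difference of 5. Power is the probability that a noncentral t with n − 1 = 21 degrees of freedom and noncentrality Δ√n/SD exceeds the critical t.

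- Two-sided .05 (critical t 2.080): SD = 6.90, noncentrality 5 × 4.690/6.896 = 3.40, power 0.90.
- One-sided .05 (critical t 1.721): SD = 7.75, noncentrality 5 × 4.690/7.750 = 3.03, power 0.90.

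**2. The same calculation at margin 4.** Only Δ changes, so the noncentrality is multiplied by 4/5.

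| Planning alpha | Noninferiority limit | Noncentrality | Power at 4 | Normal check | Pairs for 90% at 4 |
|---|---|---|---|---|---|
| two-sided .05 | two-sided .05 | 2.72 | 0.737 | Φ(0.8 × 3.2416 − 1.960) = 0.737 | 34 |
| one-sided .05 | one-sided .05 | 2.42 | 0.757 | Φ(0.8 × 2.9265 − 1.645) = 0.757 | 34 |
| two-sided .05 | one-sided .05 | 2.72 | 0.838 | Φ(0.8 × 3.2416 − 1.645) = 0.829 | 27 |

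Here 3.2416 = 1.960 + 1.2816 and 2.9265 = 1.645 + 1.2816, after rounding. In the first two rows the normal approximation needs 22 × (5/4)² = 34.4 pairs. In the third it needs 34.4 × (2.9265/3.2416)² = 28.0.

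**3. Adding P > .05.** With a true difference of 0, about 2.5% of trials give a two-sided P below .05 in favour of inorganic. These satisfy the limit of 4 but fail the P condition. The three powers fall to about 0.71, 0.73 and 0.81.

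**4. Could the 22 have come from the noninferiority formula?** With a common SD, margin 4 and 90% power, that formula would have returned about 27 to 34, and keeping the larger number would not give 22. Conversely, suppose 22 gave 90% at margin 4, one-sided. Then the standard error is 4/2.9265 = 1.367, and the power at 5, two-sided, is Φ(5/1.367 − 1.960) = 0.955, not 0.9. So the statements do not fit together under a common SD and a common power.

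**5. Dropout allowance.** The rate is not given, so take 20 evaluable pairs as an illustration. If the 0.90 at 5 applied to 20 pairs, the SD is 6.54 (two-sided) or 7.36 (one-sided). If all 22 are retained, power at 4, without the P condition, is 0.781, 0.794 and 0.871 in the order of the table. If dropout leaves 20 pairs, it is again about 0.74, 0.76 and 0.84.

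**The case against.** The strongest reply is that a noninferiority calculation was made. Sample Size Estimates says so, and says the larger sample was kept. A reader might infer from the power sentence that the trial was sized on a superiority null alone; the text does not support that. What the reply cannot do is rescue the 0.9. The formula's margin, SD and power are unreported, and step 4 shows that it does not fit with 22 under a common SD at margin 4 and 90% power. A different SD or a lower power in that formula cannot be excluded.

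A reader might also take about 0.75 as the trial's power. That is too firm. It needs the same alpha convention in both calculations. The statistical methods use a one-sided CI, and a two-sided reading of the equality test is natural; that combination gives 0.84. The dropout allowance may raise the figures to 0.78 to 0.87. The SDs of 6.9 and 7.75 are back-solved from the stated power, so they are not planning values that the authors could report as their own.

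An unpaired formula behind the 22 could leave more power: about 0.95 with one alpha convention, if the within-person correlation were 0.5. That correlation is an assumption, and the section says the means were compared in pairs.

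Finally, enrolment ended in December 2020 and analysis ran in January to March 2021, according to Results. Correcting the power changes neither the sample nor the confidence limit. That stands, and it is why the remedy is confined to wording.

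**Conclusion.** The point holds as an inconsistency between sections. The stated 0.9 belongs to a difference of 5 and a null of equal means; the trial is judged at 4, and no power at 4 is given. It should be corrected, because the published power does not describe the published decision rule.

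On its size: with 22 pairs, a true difference of 0 and 0.90 at 5, power at margin 4 is about 0.74 to 0.76 under one alpha convention and about 0.84 under the mixed one. With the P > .05 condition these become about 0.71 to 0.81. The illustrative dropout reading, without that condition, gives about 0.78 to 0.87. All these paired readings are below 0.90. If inorganic truly loses more SPF than organic, power is lower still.

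Two stronger conclusions are not supported. The article does not show a miscalculated number, since its inputs are too few to reproduce the 22. It also does not establish a single true power, since the SD, sidedness and dropout rate are missing.

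**What to change.** 1. Use one prespecified margin in Outcomes, Sample Size Estimates, and Data Management and Statistical Methods, and document when it was set, in particular whether this was before the allocation was unmasked.
2. Write the null as a mean excess SPF loss of inorganic over organic of at least that margin.
3. Replace the 0.9 with the power of 22 pairs at that margin. Compute it from the actual planning SD of paired differences, and state that SD, the sidedness of alpha and the dropout rate. Do not print a figure derived from a back-solved SD. At margin 4, expect roughly 0.74 to 0.84, and say whether the P > .05 condition is included.
4. Report the margin, SD, power and resulting sample size of the noninferiority formula, so that the choice of the larger number can be followed.

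The cost is wording and a less favourable power figure. The trial should not be enlarged, since enrolment is complete.

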**Methods:**

This study is a randomized, split-body, double-blind, noninferiority, and multicenter clinical trial in Cikini, Jakarta, Indonesia. An estimated 22 athletes in each group, who aged 18-40 years and practice in the morning or afternoon, will be randomized using a computer-generated randomization method. We calculated the sample size using the difference in the average decrease in sun protection factor (SPF) levels that is considered significant based on the clinical judgment set by the researchers, which was 5. Neither the research subjects nor the researchers are aware of the type of sunscreen that will be applied. The hypothesis will be tested using paired-sample t test or Wilcoxon to assess the difference of SPF levels in each group between organic and inorganic sunscreens with SPSS (version 20.0; IBM Corp).

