### Study Design and Setting

This is a randomized, split-body, double-blind, noninferiority, multicenter clinical trial. The recruiting center is Cikini swimming pool, located in Jakarta, Indonesia. Recruitment began in August 2020 and ended in December 2020.

Research subjects were selected from Cikini swimming center in Jakarta, Indonesia. Data collection will be carried out on the same person using the split-body method. Each research subject will receive 2 treatments in the form of inorganic and organic sunscreens. The sunscreen application will be executed on the back area on the right and left for each treatment simultaneously.

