## Discussion

We developed a protocol for a randomized, split-body, double-blind, noninferiority clinical trial to evaluate the persistence of the inorganic versus organic sunscreens in the outdoor swimmers with estimated 22 participants in each group. This study aims to assess whether inorganic sunscreen is as good as organic sunscreen in the field of the resistance of sunscreens after swimming for 1.5 hours of training. The secondary objectives are SPF value resulting from in vivo method, which types of sunscreens provide higher persistence.

COVID-19 health protocol during the pandemic will be conducted. Before data collection begins, we will conduct a preliminary and inter-reviewer reliability testing. The instrument will be calibrated first before use at each session of data collection. All subjects had to sign the consent form if they are willing to participate. Irradiation test will be done and then followed by SPF measurement of the sunscreens developed by PT Paragon Technology and Innovation in the form of an oil-in-water emulsion. The study medication must be discontinued if suspected adverse events occur or if patient consent for participation is withdrawn. Research subjects will be excluded from the study, but their recovery will be followed by researchers.

The collected data will be analyzed using SPSS (version 20.0; IBM Corp). This clinical trial has been approved by the ethic committee and registered to ClinicalTrials.gov. Study results will be disseminated through publications in the Open Access format. This study will provide information about SPF 30 persistence in sunscreens and the best type of sunscreen to be used while swimming, particularly to athletes.

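### Size and power are worded for 22 experimental plus 22 control subjects, which contradicts the split-body design and does not tie the 0.9 to the paired noninferiority test at 4 SPF

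*Protocol article*

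**What the plan says.** The design is within-person. Study Design and Setting states "Data collection will be carried out on the same person using the split-body method" and "Each research subject will receive 2 treatments in the form of inorganic and organic sunscreens". The Blinding section numbers the right and left back of each subject as the two areas to be allocated.

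The size is nevertheless stated by group, in three places:

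- Abstract, Methods: "An estimated 22 athletes in each group".
- Sample Size Estimates: "we estimated a minimum sample size of 22 participants in each group", and then "In total, 22 experimental subjects and 22 control subjects will be adequate to reject the null hypothesis". The null given there is equality of the experimental and control means, with power 0.9 and type I error 0.05. The difference used is 5 SPF.
- Discussion: "with estimated 22 participants in each group".

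Sample Size Estimates also says that two formulas were used, "the continuous variable noninferiority test formula and the comparison of the mean of the 2 groups in pairs", and continues: "From the 2 formulas, the largest number of samples was taken for further use in research". It does not say which of the two gave 22.

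The planned analysis, in Outcomes and in Data Management and Statistical Methods, is a paired t test or Wilcoxon test with a one-sided confidence interval. The confidence limit is compared with 4 SPF.

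**The concern.** A split-body trial has athletes, each supplying one pair of measurements. It has no separate control subjects. The power sentence therefore differs from the planned analysis in three ways:

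- **Unit:** two sets of subjects rather than pairs.
- **Null hypothesis:** equal means rather than inferiority by at least the margin.
- **Difference:** 5 SPF rather than 4.

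Two things are at stake. A reader cannot tell from the text how many athletes were planned, and so cannot judge whether the trial reached its size. Nor can a reader take 0.9 as the chance that the trial shows noninferiority when the products are truly equal, which is the figure that matters when the result is interpreted.

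**Working it through.** **Inputs from the article.** 22 per group, power 0.9, type I error 0.05 (sidedness not given in the sample-size section), difference 5, decision limit 4, one-sided interval in the analysis. No SD, within-athlete correlation or dropout rate is given.

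**Reproducing 22 and 0.9.** Without an SD this cannot be done forwards. One can only solve for the SD that makes 22 give 0.90. The figures below use the noncentral t unless stated, ignore dropout, and take the true difference as 0 when power is evaluated at the margin.

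**Step 1: if 22 came from an independent-groups formula.** The noncentrality is 5 / (SD × √(2/22)) on 42 degrees of freedom. Power 0.90 requires a per-product SD of 4.997 (two-sided .05) or 5.574 (one-sided .05).

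**Step 2: the effect of pairing alone.** Keep the difference at 5 and the same sidedness, and analyse 22 pairs. The SD of the difference is SD_d = SD × √(2(1 − ρ)). The noncentrality is 5 / (SD_d / √22) on 21 degrees of freedom.

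| Assumed ρ | SD_d, two-sided case | Power at 5 | SD_d, one-sided case | Power at 5 |
|---|---|---|---|---|
| 0 | 4.997 × √2 = 7.07 | 0.89 | 5.574 × √2 = 7.88 | 0.89 |
| 0.3 | 4.997 × √1.4 = 5.91 | 0.97 | 5.574 × √1.4 = 6.60 | 0.96 |
| 0.5 | 4.997 × √1 = 5.00 | 0.99 | 5.574 × √1 = 5.57 | 0.99 |

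At ρ = 0 the loss from 0.90 to 0.89 is only the change from 42 to 21 degrees of freedom. Any appreciable positive correlation raises power above 0.90. Only a negative correlation lowers it materially.

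**Step 3: the effect of the limit of 4.** Test the same 22 pairs one-sided at .05 against 4. Power at ρ = 0, 0.3 and 0.5 is 0.82, 0.92 and 0.98 if the SD was 4.997, and 0.74, 0.87 and 0.95 if it was 5.574.

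**Step 4: if 22 came from the paired formula.** The noncentrality 5 / (SD_d / √22) gives power 0.90 when SD_d is 7.75 (one-sided) or 6.90 (two-sided). Against the limit of 4, one-sided .05:

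- SD_d = 7.75: noncentrality 4 / (7.75 / √22) = 2.42, power about 0.76.
- SD_d = 6.90: noncentrality 4 / (6.90 / √22) = 2.72, power about 0.84.

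**Step 5: why 22 or 44 matters.** Take the one-sided paired case by normal approximation. The SD_d giving 0.90 at 5 with 22 pairs is 5 × √22 / (1.645 + 1.282) = 8.01. With 44 athletes, power at 4 is Φ(4 × √44 / 8.01 − 1.645), about 0.95. With 22 it is about 0.76. The two readings of the text are far apart.

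**The case against.** The best defence is that the same section names a formula for means in pairs. The figure 22 may then be the number of pairs, and 0.9 may be the power of a paired test. Because each person is treated on both sides of the back, 22 in each group reads naturally as 22 treated sides per product, which is 22 athletes. Both arguments stand. A reader might infer that neither 22 nor 0.9 can belong to a split-body design. The article does not support that: with no SD and no statement of which formula gave 22, it can be neither confirmed nor refuted.

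A second defence is that independent-groups planning is roughly neutral or conservative for a paired analysis. Step 2 bears this out at a difference of 5 for non-negative correlation. The group wording alone does not endanger power.

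Third, a condensed article may leave the SD, the dropout rate and the formula to the full protocol. Their absence is not the complaint, and no miscalculation has been shown. The defect is that the text which is printed describes a different design and null from those of the trial.

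A reader might also take the powers in Steps 3 and 4 as limits on the true power. They are not. They rest on assumed correlations and back-solved SDs. Step 3 would give 0.995 or more at a correlation of 0.7, and 0.68 to 0.76 at −0.2.

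**Conclusion.** The point holds as a contradiction in the text. The sample-size statement, echoed in the Abstract and the Discussion, is worded for two sets of subjects and a null of equal means at 5 SPF. The design section describes one set of athletes treated with both products, and the analysis sections describe a paired noninferiority comparison at 4 SPF. The number of athletes is left to inference, and 0.9 is not shown to be the power of the planned test.

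The pairing costs almost nothing. The larger effect, if there is one, comes from planning at 5 and deciding at 4: a nominal 0.90 becomes about 0.76, or about 0.84 if the planning test was two-sided. Both figures assume that 22 is the number of evaluable pairs, that the true difference is 0 and that the test is one-sided at .05. They illustrate the size of the effect and do not establish that the trial is underpowered. The statement should be corrected, but the design is not invalid because of it.

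**What to change.** In the Abstract, Sample Size Estimates and Discussion, replace the per-group wording, and the split into experimental and control subjects, with the number of athletes, each receiving both products: 22 pairs, or the actual planned number if it differs.

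Replace the sentence giving power 0.9 with the power of the one-sided paired noninferiority test at the margin of 4. Compute it from the planning SD of the within-athlete difference in SPF decrease, and say which formula gave the number.

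The cost is rewording and one recalculation. The restated power may be less favourable than 0.9. Enrolment closed in December 2020, so this is a reporting correction and needs no further enrolment.

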### Recruitment

Researchers will conduct COVID-19–related health protocols when collecting data in the context of preventing the pandemic spread. The body temperature and oxygen saturation of the research subjects will be checked before the examination. Each subject will be given a mask and face shield and asked to wash their hands. Researchers will provide the instructions to maintain a distance of at least 1 m during data collection. We will limit the number of subjects, only 4 athletes per day, to attend each sampling session. Before and after the test of each research subject, the tools will be cleaned using an alcohol swab.

### Allocation of Sequence Generation and Concealment Mechanism

Treatment allocation is applied by computer-based randomization [9] to determine the back area and type of sunscreen provided [10]. The allocation data for each subject will be placed in a nontransparent, sealed envelope along with sunscreen. At the time of data collection, the envelope will be opened, and sunscreen will be applied by the research assistant. Both randomization and treatment allocation will be carried out by statisticians who were not known by the researchers or the research subjects. The data will not be accessed until data collection for all subjects is completed.

